**Figure 1 F1:**
[figure not shown]
**Study design. **^*^Two consecutive measurements at least 1 day apart. CKD, chronic kidney disease.

Each study visit consists of a fasting blood draw (last food intake including the study medication should be at least 8 hours before) and urinalysis, measurement of vital signs, and assessment of changes in concomitant medication and adverse events (Table 1). At the beginning of the study a physical examination will be done and body weight and height will be assessed. Study visits will be performed at weeks 4, 8, 12, 20, 29, 38, 47, 60, 73, 86, and 104.

**Table 1 T1:** Visit and assessment schedule

	**Screening period (4 weeks)**							**Treatment period (0 to 24 months)**					
		**Day 0**	**Week 4**	**Week 8**	**Week 12**	**Week 20**	**Week 29**	**Week 38**	**Week 47**	**Week 60**	**Week 73**	**Week 86**	**Week 104**
			**(± 2 days)**	**(± 2 days)**	**(± 2 days)**	**(± 5 days)**	**(± 5 days)**	**(± 5 days)**	**(± 5 days)**	**(± 10 days)**	**(± 10 days)**	**(± 10 days)**	**(± 10 days)**
**Visit**	1	2	3	4	5	6	7	8	9	10	11	12	13
**Informed consent**		x											
**Inclusion/exclusion criteria**	x	x											
**Randomization**		x											
**Medical history**		x											x
**Concomitant medication**		x	x	x	x	x	x	x	x	x	x	x	x
**Physical examination**		x											x
**Body weight and height**		x											x
**Vital signs (BP, PR)**		x	x	x	x	x	x	x	x	x	x	x	x
**Laboratory test**	x	x	x	x	x	x	x	x	x	x	x	x	x
**Laboratory test: bone markers**		x				x							x
**Biobank sample**		x				x			x		x		x
**Urinalysis**	x	x	x	x	x	x	x	x	x	x	x	x	x
**24-hour urine collection**	x^a^	x^a^	x			x			x				x
**Urine pregnancy test**^**b**^		x	x	x	x	x	x	x	x	x	x	x	x
**Adverse events**			x	x	x	x	x	x	x	x	x	x	

^**a**^To be performed either at screening visit 1 or screening visit 2. prior to randomization; ^**b**^for females of childbearing age only. BP, blood pressure; PR, pulse rate.

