### Sample size

Assuming equal baseline levels of eGFR between the two study groups, a clinically relevant difference of 5 ml in eGFR after 2 years, and an estimated standard deviation of 12 ml for the change in eGFR after 2 years (pilot data, Figure 2), an independent sample *t*-test with a sample size of 2 × 100 patients will give 80% power to reach statistical significance at a two-sided significance level of 5%.

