### Statistical methods

The intention-to-treat population will be used for statistical analysis. The primary analysis focuses on the estimated treatment effect at 2 years (difference between the two groups in eGFR after two years), which will be provided as the point estimate at the expected difference, 95% confidence interval and *P*-value. Mortality of patients or other reasons for dropout will be addressed by jointly modeling longitudinal eGFR and time to death using an appropriate joint model for longitudinal and time-to-event outcome [37]. In the longitudinal part of this model, a linear mixed model will be used with the repeated eGFR measurements as outcome values, and including as fixed factors treatment group, all stratification criteria (age, diabetes, severity of acidosis, previous alkali treatment), the eGFR baseline value and time since start of treatment, and a random intercept. An interaction effect (product term) of the treatment group and the time since start of treatment will also be included. Graphical diagnostic tools (residual plots) will be used to confirm the adequacy of model assumptions. A secondary outcome is time to death, compared between the treatment groups, which will also be estimated by the joint modeling approach. The time up to the point of need of RRT will be compared between the two treatment groups, accounting for death as a competing risk, by modeling the cumulative incidence function [38], including treatment group and the covariates age, diabetes, severity of acidosis and baseline eGFR. Percent change (from baseline to week 20 and baseline to week 104, respectively) in markers of bone metabolism will be analyzed by analysis of covariance, to adjust for sex, age, change in renal function, and baseline values of the bone markers. The incidence of serious adverse events will be reported and compared between groups using the chi-squared test. Baseline parameters (etiology of CKD, relevant medical disease, age, gender, concomitant medication, blood pressure, number of antihypertensive medications, and laboratory measurements) will be analyzed descriptively for the interventional and control group, respectively. SAS (Version 9.3, SAS Institute Inc., Cary, NC, USA, 2011) will be used for data management and analysis, and R 2.12.2/package JM [37] will be used for the main outcome analysis.

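### The primary joint model names a random intercept as its only random effect, so its standard error for the 2-year eGFR difference is too small, by an amount that depends on a visit SD the protocol does not give

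*Protocol article*

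**What the plan says.** The Statistical methods section of the protocol article makes the primary result the "difference between the two groups in eGFR after two years", estimated from a joint model of repeated eGFR and time to death. The longitudinal part is a linear mixed model. Its fixed effects are arm and the four stratification factors, and the list closes with "the eGFR baseline value and time since start of treatment, and a random intercept". The section then adds: "An interaction effect (product term) of the treatment group and the time since start of treatment will also be included". It names no random slope, serial correlation or robust variance. Residual plots are promised, but no action follows a poor plot and no fallback model is given.

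The visit schedule supplies the repeated values: "Study visits will be performed at weeks 4, 8, 12, 20, 29, 38, 47, 60, 73, 86, and 104".

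The Sample size section sets its target effect as "a clinically relevant difference of 5 ml in eGFR after 2 years". For the spread, the pilot cohort supplies "an estimated standard deviation of 12 ml for the change in eGFR after 2 years". The section concludes that "an independent sample *t*-test with a sample size of 2 × 100 patients will give 80% power".

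**The concern.** In this model the treatment difference at 2 years is the arm coefficient plus twice the arm-by-time coefficient. A random intercept lets each patient's line sit higher or lower, but all lines within an arm stay parallel. A patient who loses eGFR faster than the arm average drifts steadily away from the fitted line. The model reads that drift as unrelated errors at separate visits. It therefore credits 200 × 11 = 2,200 visit values with more information about slope than 200 patients can supply.

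The primary confidence interval would then be too narrow and the P-value too small, so a treatment with no effect would be declared effective more often than the stated 5%.

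The joint model is also there to deal with death and dropout. Without a patient-level slope, a patient's own decline can reach the survival part only through a shift in the predicted intercept, which weakens that adjustment.

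**Working it through.** **1. The plan's own figure.** The two-sample t-test has SE = 12 × √(2/100) = 1.70 mL and noncentrality 5/1.70 = 2.95. Power is 83.4% (noncentral t) against the stated 80%, and 92 per arm would give 80%. The gap is on the conservative side and does not bear on this point. The SE of 1.70 is a useful yardstick.

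**2. Splitting the SD of 12.** Let σ be the within-patient visit SD and τ the SD of true slopes per year. With linear individual trajectories, the 2-year change has variance 4τ² + 2σ² = 144. A model without τ must put everything into σ, which gives σ = 12/√2 = 8.5 mL at every visit. The protocol gives no σ, so a range is used.

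**3. Design constants.** The 11 visits, in years (weeks/52), have mean 0.841 and sum of squares about the mean S = 4.152. The contrast at 2 years is the arm difference in mean level plus (2 − 0.841) = 1.159 times the arm difference in slope; 1.159² = 1.343. There are 100 patients per arm, so the multiplier is 2/100 = 0.02.

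**4. Worked case, σ = 4.** τ² = (144 − 32)/4 = 28, so τ = 5.29 per year. Assume an SD of 11 mL between patients at baseline. The variance of the true starting level, given measured baseline, is then 121 × 16/(121 + 16) = 14.13.

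- Variance of a patient's mean level: 14.13 + 28 × 0.841² + 16/11 = 35.39.
- Residual variance as the random-intercept model sees it: 16 + 28 × 4.152/10 = 27.6.
- Model SE: √[0.02 × (35.39 + 1.343 × 27.6/4.152)] = 0.94.
- True SE: √[0.02 × (14.13 + 4 × 28 + 16 × (1/11 + 1.343/4.152))] = 1.63.
- Type I error: 2Φ(−1.96 × 0.94/1.63) = 26%.

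**5. The range, with the SD of change held at 12.** Simulation used 2,000 null trials per setting.

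| Visit SD σ | Slope SD τ (per year) | Model SE | True SE | Type I error | Simulated |
|---|---|---|---|---|---|
| 3 | 5.61 | 0.88 | 1.66 | 30% | 29% |
| 4 | 5.29 | 0.94 | 1.63 | 26% | 24.5% |
| 5 | 4.85 | 1.01 | 1.58 | 21% | 21% |
| 6 | 4.24 | 1.08 | 1.51 | 16% | 16% |
| 7 | 3.39 | 1.14 | 1.42 | 12% | 11% |
| 8 | 2.00 | 1.20 | 1.30 | 7% | not run |
| 8.5 | about 0 | 1.22 | 1.22 | 5% | 4% |

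**6. Dropping the SD of 12.** The Discussion says that 9% of the treated arm of a cited trial lost more than 3 mL/min per year, with a mean loss of 1.88/2 = 0.94 per year. If slopes are normal, τ = (3 − 0.94)/1.34 ≈ 1.5 per year. Type I error is then 11%, 9%, 8% and 7% for σ = 3, 4, 5 and 6.

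**7. Robustness.** With 20% random dropout, the error is 28% (σ = 4) and 17% (σ = 6). With random-walk deviations in place of linear slopes, it runs from 26% to 15% for σ = 3 to 6.

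**8. After the change.** A two-stage equivalent of a random intercept and slope gave 4.7% to 5.7% for σ = 3 to 7 (4,000 trials each). A direct fit at σ = 4 (265 trials) gave 4.2% with the random slope and 20% without it in the same trials.

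**The case against.** The size of the inflation rests on a visit SD that appears nowhere in the protocol. The Sample size section gives one total SD from a pilot cohort, and its split into slope variation and visit noise is unknown. A reader might infer that noise cannot produce an SD of 12, or that the error rate is a settled multiple of 5%. The document supports neither. Noise of 8.5 mL would produce it, although that is implausible for patients enrolled at eGFR 15 to 60, and the error falls to 7% at a visit SD of 8 mL. The cited trial also points to a smaller slope spread, though it measured creatinine clearance and the reading assumes normality. This objection stands, and the result must be given as a conditional range.

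A reader might also infer that the joint model cannot link a patient's decline to death. That is too strong. A fast decliner's values lie below the arm mean, so the predicted intercept falls and some association remains. The link is weakened, not absent, and it was not simulated.

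Third, the article is condensed, the word "only" is not in its text, and it promises a suitable joint model and residual plots. But it writes out the random part and names nothing beyond the intercept. A poor plot triggers no stated action, and changing the primary model after seeing open-label data carries its own risk of bias. This softens the point without answering it.

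Finally, simulated patients with such wide slopes can reach impossible values: about 4% have a true eGFR below zero at week 104. Ending follow-up below an assumed eGFR of 10 lowered the error only from 27% to 23%.

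**Conclusion.** The concern holds, and the model is wrong as written. With the protocol's SD of 12 mL, 100 patients per arm and the 11 visits, the model SE is about 53% to 80% of the true one (0.88/1.66 to 1.14/1.42). The type I error is about 30% down to 12% for an assumed visit SD of 3 to 7 mL. It returns to 5% only when all of the SD of 12 is visit noise. With a slope SD of about 1.5 per year, and so without the SD of 12, the error is about 7% to 11% for visit SDs of 6 down to 3 mL. The direction is the same wherever slopes vary between patients; the size is not fixed by the document.

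The calculation covers the longitudinal part alone. The survival link adds no patient-level slope and the SE remains model-based, so there is no reason to expect the joint fit to remove the problem.

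**What to change.** In the Statistical methods section, replace the random intercept with a random intercept and a random slope for time, with unstructured covariance. Keep the fixed effects and estimate the week-104 treatment contrast from that model. State in advance that, if it does not converge, a simpler covariance that still keeps the random slope will be used, for example uncorrelated intercept and slope.

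This changes one phrase and needs no new data, visits or patients. The confidence interval becomes wider, which is its honest width, and fitting may take more effort. Power for 5 mL, without dropout, remains 84% to 94% for visit SDs of 3 to 7 mL.

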	**Daily sodium bicarbonate (Nephrotrans® 840 mg) dosage**	
**(A) Baseline treatment algorithm**	Investigational group	Control group
Mean HCO_3_^-^ of two measurements		
<18 mmol/L	5,040 mg (2 capsules TID)	2,520 mg (1 capsule TID)
18 to 19 mmol/L	4,200 mg (2 capsules BID, 1 capsule QD)	1,680 mg (1 capsule BID)
19.1 to 20.0 mmol/L	2,520 mg (1 capsule TID)	Monitor
>20 mmol/L	1,680 mg (1 capsule BID)	
**(B) Follow-up visit treatment algorithm**	Investigational group and control group	
Difference to target HCO_3_^-^ level		
−1 mmol/L	Add 1,680 mg to the previous daily dosage (+1 capsule BID)	
−2 mmol/L	Add 3,360 mg to the previous daily dosage (+2 capsules BID)	
≤ −3 mmol/L	Add 5,040 mg to the previous daily dosage (+2 capsules TID)	
+1 mmol/L	Subduct 1,680 mg from the previous daily dosage (−2 capsules)	
+2 mmol/L	Subduct 3,360 mg from the previous daily dosage (−4 capsules)	
≥ +3 mmol/L	Subduct 5,040 mg from the previous daily dosage (−6 capsules)	

QD, every day; BID, twice daily; TID, trice daily.

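### The primary model can use more of the pre-randomisation data: derive baseline eGFR as the mean of the available values and add continuous age and bicarbonate (small precision gain, no effect on validity)

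*Protocol article*

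**What the plan says.** - **Covariates.** Statistical methods lists the fixed effects of the linear mixed model: treatment group, "all stratification criteria (age, diabetes, severity of acidosis, previous alkali treatment"), then "the eGFR baseline value and time since start of treatment, and a random intercept", plus a treatment-by-time term. The sample or samples behind the baseline eGFR are not named.
- **Cuts.** Randomization and study visits defines the age criterion as above 60 years versus 60 or below, and the acidosis criterion as bicarbonate below 18 mmol/L versus 18 or above. Statistical methods does not state the coding, but two-level factors are the natural reading.
- **Samples before randomisation.** Table 1 marks a laboratory test, and the check of inclusion and exclusion criteria, at both the screening visit and day 0. Participants requires an MDRD eGFR for entry.
- **Averaging elsewhere.** The starting-dose table (Table 2A) is entered with "Mean HCO_3_^-^ of two measurements". No similar rule is given for eGFR.
- **Sample size.** "a clinically relevant difference of 5 ml in eGFR after 2 years", "an estimated standard deviation of 12 ml for the change in eGFR after 2 years", and "an independent sample *t*-test with a sample size of 2 × 100 patients will give 80% power", two-sided 5%.

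**The concern.** Baseline eGFR is likely to be the strongest predictor of eGFR at 2 years. One creatinine-based value carries visit-to-visit error, and that error leaves some between-patient variance in the treatment comparison. The mean of two values has half the error variance when the errors are independent. In the same way, a factor cut at 60 years or 18 mmol/L carries only part of the prognostic information in the underlying value.

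What is at stake is precision. All of this information precedes randomisation, so using it or not using it biases nothing.

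**Working it through.** **1. The plan's own figure.** Inputs from Sample size: difference 5, SD 12, two-sided 5%.

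n per arm = 2 × (1.960 + 0.842)² × 12² / 5² = 90.4, so 91 (92 by exact t-test) for 80% power. With 100 per arm the SE is 12 × √(2/100) = 1.697, and power is 83.8% (normal) or 83.4% (t). The stated 80% is therefore on the conservative side before any dropout. No dropout allowance is stated.

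**2. Variance of the 2-year difference with one or two baseline values.** Assumptions:
- each patient has a true baseline (between-patient SD τ), a true slope and independent visit errors (SD s);
- true change is independent of true baseline;
- follow-up is complete;
- the plan's SD of 12 is for a single-value change, so 4·Var(slope) + 2s² = 144.

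The article gives neither τ nor s. I use τ = 8–12 mL and s = 2–6 mL.

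With m baseline values averaged, the per-patient variance at 2 years is

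V(m) = τ²(s²/m) / (τ² + s²/m) + (144 − 2s²) + L·s²

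L is the leverage at 2 years of a line through the 11 scheduled visits (weeks 4 to 104). The mean visit time is 0.841 years and the sum of squares is 4.152, so L = 1/11 + (2 − 0.841)²/4.152 = 0.4145.

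*Example, τ = 10, s = 4:*
- m = 1: 13.79 + 112 + 6.63 = 132.4; SE = √(2 × 132.4/100) = 1.627; power 86.7%
- m = 2: 7.41 + 112 + 6.63 = 126.0; SE = 1.588; power 88.3%
- Variance falls by 4.8%, worth about 10 patients of 200.

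*Grid over τ = 8–12:*

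| s (mL) | Variance reduction | Power gain (points) |
|---|---|---|
| 2 | 1.3–1.4% | about 0.5 |
| 3 | 2.7–3.0% | 0.9–1.0 |
| 4 | 4.3–5.1% | 1.4–1.7 |
| 5 | 6.2–7.8% | 1.8–2.4 |
| 6 | 8.2–11.1% | 1.9–2.9 |

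**3. Correlated errors.** Two samples taken within a 4-week screening period may share error. With correlation 0.5 the error variance of the mean is s²(1 + 0.5)/2 = 0.75s² instead of 0.5s². In the example V becomes 129.4, and the reduction drops from 4.8% to 2.3%.

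**4. Continuous age and bicarbonate.** For a normally distributed covariate with a linear effect, a cut with proportion p above it keeps φ(c)²/[p(1 − p)] of the R²: 64% for a median cut, 49% for a 20% tail. If the partial R² is 1–5% (assumed), replacing the cut by the continuous value lowers the variance by a further 0.4–2.6% per covariate.

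**The case against.** The strongest objection is that nothing here is an error. Statistical methods does not say that the baseline is a single sample; a mean of two is also one baseline value, and the derivation is something an article may leave to the full plan. Table 1 marks a generic laboratory test, and only bicarbonate is explicitly required twice. Adjusting for the minimisation factors as used in allocation is accepted practice. Averaging bicarbonate for dosing creates no contradiction with the eGFR covariate. All of this stands, and it limits the point to a suggestion about precision.

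A reader might infer that the plan rests its main covariate on one noisy creatinine result; the text does not say so. A reader might also infer that the trial has little power in reserve. The plan's own inputs give 83–84% rather than 80%, and the adjusted repeated-measures model does better still, although dropout would reduce that margin.

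A further objection is that alkali-treated patients enter after a 4-week wash-out and screening also lasts 4 weeks, so a screening sample may precede the end of wash-out and not be exchangeable with day 0. That also stands. Since both samples precede randomisation, it trims the gain and causes no bias, and the derivation rule can deal with it.

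**Conclusion.** The point holds as a low-priority efficiency improvement. The stated covariate set names one baseline eGFR term of unstated derivation and, on the natural reading, two dichotomised factors, while fuller pre-randomisation data are very likely on file. The expected gain from averaging eGFR is about 3–5% of the variance of the 2-year difference, or roughly 1 to 1.5 power points, under an assumed within-patient SD of 3–4 mL and independent errors. The continuous covariates may add somewhat more, but that rests on assumed partial R² values.

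It would go too far to read this as precision thrown away, or as a flaw in the estimate. The model already captures most of the available gain through baseline adjustment and 11 repeated measurements.

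**What to change.** In Statistical methods, or in the statistical analysis plan before any outcome data are examined:

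1. Define baseline eGFR as the mean of the available pre-randomisation values (screening and day 0). Use day 0 alone where the screening sample is missing or precedes the end of alkali wash-out.
2. Keep all minimisation factors as used in allocation, and add age and mean baseline bicarbonate as continuous covariates beside them.

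First confirm that creatinine is part of the laboratory test at both visits. The cost is one derived variable and a few words, with no new visits, samples or patients. In an open-label trial, fixing the derivation in advance also removes an avoidable analyst choice.

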**Methods/Design:**

The SoBic-study is a single-center, randomized, controlled, open-label clinical phase IV study performed at the nephrological outpatient service of the Medical University of Vienna. Two-hundred patients classified to CKD stage 3 or 4 with two separate measurements of HCO_3_^-^ of <21 mmol/L will be 1:1 randomized to either receive a high dose of oral sodium bicarbonate with a serum target HCO_3_^-^ level of 24 ± 1 mmol/L or receive a rescue therapy of sodium bicarbonate with a serum target level of 20 ± 1 mmol/L. The follow up will be for two years. The primary outcome is the effect of sodium bicarbonate supplementation on renal function measured by means of estimated glomerular filtration rates (4-variable-MDRD-equation) after two years. Secondary outcomes are change in markers of bone metabolism between groups, death rates between groups, and the number of subjects proceeding to renal replacement therapy across groups. Adverse events, such as worsening of arterial hypertension due to the additional sodium consumption, will be accurately monitored.

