## Background

Chronic kidney disease (CKD) occurs in approximately one in ten persons worldwide and represents not only a medical challenge but also a great socioeconomic burden. Major efforts have been made to investigate treatment options aiming to slow progression to end-stage renal disease (ESRD) and, subsequently, to reduce mortality in kidney patients. A renin-angiotensin system blockade with either angiotensin-I-converting enzyme inhibitors or angiotensin-II-receptor antagonists slows the progression of decline in renal function [1-5]. However, further therapeutic interventions have not shown any benefits [6-10]. The comprehensive summery by Fink *et al.* underscores the lack of evidence-based treatment concepts in CKD and even calls screening and monitoring for early-stage CKD into question [11].

Overt chronic metabolic acidosis in CKD patients develops after a drop in glomerular filtration rate (GFR) to less than approximately 25 mL/min/1.73 m^2^. The pathogenic mechanism seems to be a lack of tubular bicarbonate production, which in healthy individuals neutralizes the acid net production. As shown in several animal and human studies the acidotic milieu alters bone and vitamin D metabolism [12], induces muscle wasting [13], and impairs albumin synthesis [14], in addition to other detrimental effects [15,16]. Experiments in rats suggest that even in the earlier stages of CKD with serum bicarbonate levels within normal limits, increased per-nephron acidification occurs to obviate overt metabolic acidosis [17]. Investigations to elucidate the contribution to the progression of CKD itself have provided contradictory results [18-20]. However, there is evidence that the alternative complement system is activated by increased tubular ammonia production [21] and that endothelin, angiotensin II and aldosteron kidney concentrations are increased as a direct result of distal nephron acidification [17,20,22]. Taken together, these alterations induce tubulointerstitial scarring in the long term.

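### Time to death is compared only through the joint model, whose treatment coefficient, under a current-value or slope link, omits any survival effect acting through preserved eGFR

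*Protocol article*

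**What the plan says.** The abstract of the protocol article lists among the secondary outcomes "death rates between groups, and the number of subjects proceeding to renal replacement therapy across groups". The section on outcome parameters also lists death as secondary.

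The Statistical methods section handles death and other dropout in the primary analysis by "jointly modeling longitudinal eGFR and time to death using an appropriate joint model for longitudinal and time-to-event outcome". It then describes the longitudinal part: "a linear mixed model will be used with the repeated eGFR measurements as outcome values, and including as fixed factors treatment group", together with the minimisation factors, baseline eGFR, time and a random intercept. It adds: "An interaction effect (product term) of the treatment group and the time since start of treatment will also be included". The death comparison is attached to the same model: "A secondary outcome is time to death, compared between the treatment groups, which will also be estimated by the joint modeling approach".

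The event part is not described. The article gives neither its covariates, nor the way eGFR enters the hazard, nor the quantity that will serve as the comparison between groups. It names no log-rank test, Cox model or Kaplan-Meier comparison for death. Time to renal replacement therapy is treated differently: the same section gives it a cumulative incidence model with treatment and baseline covariates only.

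**The concern.** The outcome is a comparison of death between randomised groups, so the natural target is the total effect of assignment. A joint model whose hazard contains modelled eGFR does not give that effect as a single coefficient. Treatment and its product with time are both in the eGFR part, so modelled eGFR already carries the treatment effect. Conditioning the hazard on it leaves in the treatment coefficient only what bicarbonate does at equal eGFR.

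This matters here because a pathway through the kidney is part of the rationale. The Background describes the aim of treatment research in this disease as "to slow progression to end-stage renal disease (ESRD) and, subsequently, to reduce mortality in kidney patients", and the trial is sized on an eGFR benefit. If the trial's hypothesis is right and lower eGFR raises mortality, reading that coefficient as the death result would leave out the expected part of the benefit. If treatment preserved eGFR but did harm by another route, the coefficient would misstate the net risk in the other direction. Follow-up eGFR is also a consequence of treatment, so a coefficient conditional on it no longer has the full protection of randomisation.

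**Working it through.** **The plan's own figure.** There is none for death: the article gives no death rate, no link between eGFR and mortality, and no power for this outcome. The only figure used from it is the 5 ml between-group difference at two years in the Sample size section.

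**Algebra under a current-value link.** Let D(t) be the treatment difference in modelled eGFR at time t, γ the treatment coefficient in the hazard, and α the change in log hazard per 1 ml higher eGFR (negative if low eGFR is harmful). Then

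log HR_total(t) = γ + α × D(t).

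The coefficient is γ, and the omitted part is α × D(t). Under a slope link, D(t) is replaced by the difference in slopes. That difference is also non-zero by arm, because the product of treatment and time is in the model. Under a shared random-intercept link, the treatment-driven change in eGFR does not enter the hazard, and the problem does not arise.

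**Size (current-value link).** Assumptions: no eGFR difference at the start, linear growth to 5 ml at month 24, and α = −0.03, −0.05 or −0.07 per ml. The time-averaged difference is 5/2 = 2.5 ml.

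| Assumed slope per 1 ml | Omitted HR, follow-up average: exp(α × 2.5) | Omitted HR, month 24: exp(α × 5) |
|---|---|---|
| 3% | exp(−0.075) = 0.93 | exp(−0.15) = 0.86 |
| 5% | exp(−0.125) = 0.88 | exp(−0.25) = 0.78 |
| 7% | exp(−0.175) = 0.84 | exp(−0.35) = 0.70 |

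If D(t) = 0 or α = 0, the omitted HR is 1.

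**Check by simulation.** The run used 60,000 patients, monthly hazards and true eGFR taken as observed. A baseline hazard of 5% a year, an eGFR SD of 10 ml, a control decline of 3 ml a year and a treatment benefit of 2.5 ml a year were all assumed. The treatment hazard ratio was estimated with and without current eGFR in the model.

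| HR per 5 ml lower eGFR | True direct HR | Treatment HR given current eGFR | Treatment HR without it |
|---|---|---|---|
| 1.10 | 1.00 | 1.05 | 1.00 |
| 1.25 | 1.00 | 1.00 | 0.89 |
| 1.50 | 1.00 | 1.00 | 0.81 |
| 1.25 | 0.80 | 0.78 | 0.70 |

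Standard errors of the log HR were 0.022 to 0.026. In the first row both estimates lie about two standard errors above their expected values of 1.00 and 0.95, but their ratio is still 0.95. An HR of 1.25 per 5 ml corresponds to ln(1.25)/5 = 0.045 per ml, close to the middle slope in the first table. In every row the conditional estimate recovers the direct part, within sampling error, and the unconditional one also includes the part through eGFR.

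**The case against.** The strongest reply is that the article never says the hazard is conditioned on current eGFR, and never says the treatment coefficient will be the reported comparison. It asks only for a suitable joint model and spells out only the longitudinal half. A shared random-intercept link would avoid the problem. The software statement, "R 2.12.2/package JM [37] will be used for the main outcome analysis", concerns the main outcome and does not settle the link. Details of the event part are what a journal article may leave to the full protocol or analysis plan. All of this stands, so the point is conditional on the link.

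A reader might infer that the survival benefit is removed from the analysis, or that the trial will report a hazard ratio of 1.0. The documents do not support either reading. What is lost is lost from one coefficient, not from the model: the total effect can be rebuilt as γ + α × D(t), or as model-based survival by arm. A reader might also take 0.86, 0.78 and 0.70 as overall effects. They are month-24 values, and averaged over follow-up the log effect is half as large.

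The reply does not dispose of the point. The article states the target as "death rates between groups" and assigns it to a single method. In some of that method's ordinary forms, the obvious output is not the total effect. The step that would recover it is not mentioned, and a simpler method estimates the target directly. Replacing a named method with a better one is more than asking for missing detail.

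**Conclusion.** The point holds in conditional form. The joint model is the only named comparison of time to death. Under a current-value or slope link, its event-part treatment coefficient is a direct effect given eGFR, not the total effect of randomised assignment.

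The documents cannot fix the size. Under a current-value link, linear growth to 5 ml and the assumed slopes of 3% to 7% per ml, the omitted hazard ratio runs from about 0.93 to 0.84 on average over follow-up. It is zero on the log scale if the arms do not differ in eGFR, if eGFR is unrelated to death, or if only a random intercept is shared. Whether the coefficient or a combined effect would be reported is not stated, so the article does not show that a biased death result is planned. Death is a secondary outcome without a power claim, and the primary eGFR analysis is unaffected.

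**What to change.** Compare time to death in all randomised patients by a method that does not condition on follow-up eGFR. Use either a Cox model with treatment, the four minimisation factors and baseline eGFR, or a log-rank test. Choose one in advance and show Kaplan-Meier curves by arm. The curves also help if an effect grows over time, because a single hazard ratio then averages over it.

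Keep the joint model for the eGFR outcome. If its event-part treatment coefficient is reported, label it as a direct effect given eGFR and as exploratory.

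The cost is one sentence in the plan and one extra standard analysis. No new data are needed.
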